### Safety considerations, adverse events, and termination of study

Throughout the trial period, participants are encouraged to contact the study coordinator if they experience any side effects from the IHG training. In addition, during the 5-, 10-, 15-, and 20-week follow-ups all participants will be asked if they have any discomfort or encountered any harms by being part of the study. Muscle soreness may occur during and after the training sessions. This is also seen following traditional strength training and is expected to diminish within 1–2 days [21]. Furthermore, blood pressure might rise slightly during training as seen in running or swimming. Participants will be removed from the study if they start/adjust/terminate anti-hypertensive drugs during the trial. Likewise, if they die or emigrate they will be removed from the study.

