**Discussion:**

This assessor-blinded, randomized controlled trial will explore the effect of a 20-week IHG home training intervention on resting blood pressure in hypertensive older adults. In addition, the trial will report adherence and potential harms related to the IHG home training.

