Recently, we have shown that handgrip [10] and lower extremity strength [11] can be measured precisely using a standard Nintendo Wii Board (Wii) with an on-screen visual feedback of the force exerted over time (force/velocity curve). As a continuation of this work, we have further developed a novel method that monitors handgrip muscle control and is suitable for IHG home training. Given the development and low-cost nature of the Wii, we are now able to perform home-based IHG training. For the above reasons we intend to conduct a IHG training study, which will be twice as long (20 weeks) as the longest previous study (10 weeks) to explore the effects on specific measures of blood pressure and other relevant outcomes. Our primary aim is to explore the effects of 20 weeks’ IHG home training facilitated by a Wii in hypertensive older adults (50 + years of age) in lowering SBP. Secondary aims are to explore if/when a leveling-off effect on SBP will occur during the 20-week intervention period in the training group and to explore adherence and potential harms related to the IHG home training. The study will compare IHG home training with a control group in a randomized, assessor-blinded design. Thus, we hypothesize (1) that 20 weeks of IHG home training will significantly reduce SBP in hypertensive older men and women compared to usual care, (2) that a leveling-off effect on SBP will occur during the 20 weeks of IHG training, and (3) that a minimum of 50% of participants will complete at least 50% of their training sessions (30 sessions).

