### Participants and setting

The study will be conducted at one study site: Aalborg University Hospital, Department of Geriatric and Internal Medicine, Aalborg, Denmark. Participants will, therefore, primarily consist of individuals living in an urban environment. Using the criteria below, we attempt to target a study population which has a 15–20% or medium absolute risk of stroke or myocardial infarction within a 10-year period according to the Danish Hypertension Society [13]. Written informed consent will be obtained from each participant.

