### Sample size

Based on previous evidence [14], and using a more conservative approach, we carried out an a priori power analysis assuming a 7-mmHg difference in the ∆SBP between the IHG training and the usual-care group (favoring the IHG training group) after 20 weeks of training. In addition, we assumed the standard deviation of the IHG training and usual-care group to be 8 and 9 mmHg, respectively. We further choose a power of 80% and an alpha level of 5% with equal group sizes. This resulted in a total sample size of 40 participants with 20 in each group. Assuming a 25% loss to follow-up, we would need to recruit 25 participants in each group.

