**Fig. 2 Fig2:**
[figure not shown]
Illustration of the target line and the “live” applied muscle force participants will be seeing during an isometric handgrip (IHG) training session

Participants will be instructed to breathe at a normal rhythm and depth during IHG training in order to avoid Valsalva maneuvers. To ensure that participants work at 30% MVC throughout the trial, the 30% MVC will be adjusted in the intervention period (after 5, 10, and 15 weeks) according to a previously described method [10].

The usual-care group will have the same number of hospital visits for measurements of blood pressure and MVC as the intervention group in order to ensure similar attention provided by the healthcare professionals.

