#### Secondary outcome measures

Diastolic blood pressure (DBP) and heart rate (HR) will be measured using the same procedure as described above for SBP. Exerted force (maximum voluntary force, rate of force development, and force variability) will be measured in both hands using the same procedure as described in detail previously [10, 17, 18]. Further, at the end of each training session participants are asked to self-report pain intensity using a Visual Analog Scale (VAS) [19] for each hand. The VAS reports values between 0 and 10 with 0 corresponding to no pain and 10 to maximum pain. Finally, compliance of the IHG training group will be monitored by a computer-generated report every week during the intervention period.

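### Much of the harm recording depends on the participant's own view of cause, so recorded harms will not be a fair comparison between the arms

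*Protocol article*

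**What the plan says.** The section on safety considerations, adverse events and termination of study describes two routes.

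- **Between visits:** "participants are encouraged to contact the study coordinator if they experience any side effects from the IHG training".
- **At the week 5, 10, 15 and 20 visits:** "all participants will be asked if they have any discomfort or encountered any harms by being part of the study".

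The section on secondary outcome measures adds a third source. After each training session, participants score pain in each hand from 0 to 10 on a visual analog scale.

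The Background gives as part of the secondary aims "to explore adherence and potential harms related to the IHG home training", and the abstract states that "the trial will report adherence and potential harms related to the IHG home training". On contact with controls, the section on the two groups says: "The usual-care group will have the same number of hospital visits for measurements of blood pressure and MVC as the intervention group".

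**The concern.** A randomised control group shows which complaints would have occurred without training. It can do so only if events are collected in the same way in both arms, before anyone judges their cause. Here the participant judges cause first for much of what is recorded, and only one arm has training to blame.

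Two errors can follow. Background complaints may be reported more readily by trained participants, which creates an apparent excess. Events that nobody connects with gripping a board, such as a new wrist diagnosis, a fall or a hospital contact, may go unrecorded in both arms, which hides a real excess. An analysis plan cannot recover events that were never asked about.

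This matters more than usual because training is done at home and the protocol describes it as twice as long as the longest previous study.

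**Working it through.** The article states no harm rate, so there is no figure to reproduce. The check is a reading of the sources, an illustration with assumed values, and one calculation from the article's own risk figure.

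**Step 1. The three sources side by side.**

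| Source | Who can use it | Must the participant judge cause first? |
|---|---|---|
| Contact between visits | In effect the training arm only, since controls have no training to produce side effects | Yes |
| Question at four visits | Both arms, same timing and wording | Yes for harms; for discomfort the sentence can be read either way |
| Hand-pain score after each session | Training arm only | No, but it covers hand pain only |

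No source described is both free of attribution for all health events and available in both arms.

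**Step 2. How attribution changes recorded rates.** For events subject to the filter:

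recorded rate = true rate × probability that the participant attributes the event.

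The true rates and attribution probabilities below are assumptions. Expected counts use the 25 per arm to be recruited ("Assuming a 25% loss to follow-up, we would need to recruit 25 participants in each group").

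| True rate, training / control | Attribution, training / control | Recorded rate | Expected count per 25 | True difference (points) | Recorded difference (points) |
|---|---|---|---|---|---|
| 20% / 20% | 80% / 10% | 16% / 2% | 4.0 / 0.5 | 0 | 14 |
| 40% / 40% | 80% / 10% | 32% / 4% | 8.0 / 1.0 | 0 | 28 |
| 20% / 20% | 50% / 10% | 10% / 2% | 2.5 / 0.5 | 0 | 8 |
| 40% / 40% | 50% / 10% | 20% / 4% | 5.0 / 1.0 | 0 | 16 |
| 20% / 20% | 50% / 50% | 10% / 10% | 2.5 / 2.5 | 0 | 0 |
| 40% / 20% | 30% / 30% | 12% / 6% | 3.0 / 1.5 | 20 | 6 |

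First row: 0.20 × 0.80 = 0.16 and 0.20 × 0.10 = 0.02. Last row: 0.40 × 0.30 = 0.12 and 0.20 × 0.30 = 0.06.

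Unequal attribution creates a difference where none exists. Equal but low attribution shrinks a real one. With equal attribution and equal true rates, no spurious difference arises.

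**Step 3. Which events are affected in practice.** The section on participants and setting targets people with a "15–20% or medium absolute risk of stroke or myocardial infarction within a 10-year period". Assume a constant hazard and take 20 weeks as 20/52 of a year:

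- 15% risk: −ln(0.85)/10 × 20/52 = 0.00625, and 25 × 0.00625 = 0.16 expected events per arm.
- 20% risk: −ln(0.80)/10 × 20/52 = 0.00858, and 25 × 0.00858 = 0.21 expected events per arm.

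About 0.2 strokes or infarctions are expected per arm. The gain from a better question therefore lies mainly in musculoskeletal and general health events.

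**The case against.** The strongest defence is that collection is broader and more even than the two quoted sentences suggest, and that the stated aim is modest. Most of the individual points stand.

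- **Harms collected only if blamed on the study.** A reader might infer this, but the text does not support it. Discomfort can be read as unconditional, and the session pain score needs no causal judgement. The rule that removes participants who die or who start, adjust or stop anti-hypertensive drugs also implies that those events become known in both arms.
- **A control arm with almost nothing to report.** This too would be an inference. All participants are asked at the same four visits, and usual care has the same number of visits. Only the between-visit route is empty for controls.
- **A trial that cannot say whether training causes harm.** That goes too far. The aim is exploratory and concerns harms related to the training. No hypothesis concerns harms and no comparison of harms between arms is promised. Recognised local effects can be described.
- **Zero-event limits as the size of the problem.** With no events, the one-sided 95% upper limit is 1 − 0.05^(1/25) = 11.3%, or 1 − 0.05^(1/20) = 13.9% with 20. These limits come from the sample size and would be the same with a perfect question, so they do not measure this defect.
- **A journal article may paraphrase the form.** The exact script, the checklist and the recording of date and seriousness may properly sit in the full protocol, and their absence is no fault. The point rests on what the article does state.

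These arguments limit the point but do not remove it. The between-visit route is one-armed as described, and harms at visits are tied to taking part.

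**Conclusion.** The point holds in limited form. As described, recording of harms depends in large part on self-attribution and is not on an equal footing in the two arms. The trial can describe discomfort, recognised side effects and session hand pain in trained participants. It cannot give a fair controlled estimate of excess harm, least of all for events that participants do not link to training.

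The size is not known from the document. In the illustration, spurious differences run from 0 to 28 percentage points, and a true 20-point difference shrinks to 6. The direction depends on how attribution differs between arms. This rests on the assumed rates and on the article's sentences reflecting what participants will be asked. If the form already uses a neutral question, only the article's description needs correcting.

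**What to change.** At the existing week 5, 10, 15 and 20 visits, and for any contact in between, ask both arms the same question: any new or worsened symptom, new diagnosis, or contact with a doctor or hospital since the last contact, whatever the believed cause. Invite controls to call between visits on the same terms. Have the investigator judge relatedness afterwards, and report counts per arm irrespective of relatedness. Keep the session pain score as a description of the training arm.

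A neutral question also fits better with the request, in the assessment protocol, that participants not reveal their group at follow-up. The article does not say who asks about harms. If the blinded assessor does, a question about study-caused harm invites disclosure.

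The cost is one reworded question and one data-capture form. No visits are added and treatment does not change. The downside is some extra unrelated events to record in about 50 people over 20 weeks. The trial status section places the start of recruitment about a month ahead, so on that timetable the change can be made before the first participant is enrolled.

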### Assessment protocol

Prior to the randomization process, participants will undergo demographic and physiological baseline assessments by an experienced assessor. Demographic measures will include: gender, age, height, Body Mass Index (BMI), level of physical activity using the International Physical Activity Questionnaire (IPAQ) [15], co-morbidities, alcohol intake, smoking status, and number and type of medical drugs. Participants will be given advice on lifestyle changes according to the national guidelines including, but not limited to, the DASH Diet [16], reduced alcohol intake, cessation or reduction of smoking, and advice on an active lifestyle [13]. Following randomization all participants will return to Aalborg University Hospital at weeks 5, 10, 15, and 20 for follow-up assessments (see Fig. 3 for an overview based on the SPIRIT Figure) in a controlled environment. At the follow-up measures, participants will be specifically asked not to mention nor comment on which group they have been assigned to in order to maintain allocation concealment to the outcome assessor. With respect to physiological measures, these will be assessed approximately at the same time of day as the baseline measures to avoid variability due to circadian rhythms or medication intake cycle. In addition, participants will be instructed via telephone by the study coordinator to refrain from vigorous exercise and alcohol for 24 h prior to all measurements. Moreover, they will be instructed to fast and refrain from caffeine for 4 h prior to all measurements. Further, they will be instructed to refrain from smoking and intake of anti-hypertensive medicine up to 30 min prior to all measurements. In addition, the assessor will ask if the participants complied with these instructions. The noise level and room temperature (20–23 °C) will be controlled by the assessor prior to the assessments. Finally, participants will be asked to empty their bladder, if possible, before tests by the assessor.

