### Outcome measures

#### Primary outcome measure

The primary endpoint in the study is SBP, which will be measured using a standard hospital electrical sphygmomanometer (Omron Comfort M6 AC). After the participants have been relaxing for 5–10 min the SBP measurements are performed on the left arm while it is resting on a table. Participants will be instructed to sit with their legs parallel and to stay quiet during the measurements. SBP will be measured three times in the left arm with rest periods of 1 min between measurements. The average of the three measures at baseline will be used for analysis. For the home SBP recordings the participant will be asked to follow the same procedures (and use the same device) as described above and perform recordings on the same weekday and timeframe as their baseline tests at the hospital. The home measures will be performed prior to commencement of the IHG training on the relevant day.

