### Data analysis

Study data will be collected and managed using REDCap electronic data capture tools hosted at Aalborg University Hospital [20]. REDCap (Research Electronic Data Capture) is a secure web-based application designed to support data capture for research studies, providing (1) an intuitive interface for validated data entry; (2) audit trails for tracking data manipulation and export procedures; (3) automated export procedures for seamless data downloads to common statistical packages; and (4) procedures for importing data from external sources. In addition, the study has been reported to the Danish Data Protection authorities.

Statistical analysis of data will be performed using SPSS (Version 22, IBM Corporation, Armonk, NY, USA). Prior to all statistical analysis the dataset will be explored according to parametric test assumptions, and, if violated, an appropriate transformation or statistical method will be applied. Further, statistical analysis will be conducted according to the intention-to-treat principal. However, a sensitivity analysis using the per-protocol principal will also be performed. This will only include participants who have completed minimum 50% of their training sessions (480 min). The between-group difference in the ∆ change from baseline to the 20-week follow-up mark for the primary endpoint will be analyzed using a linear mixed-effects model. Secondary outcomes will also be analyzed using a linear mixed-effects model. Besides these primary analyses a number of sub-analysis will also be performed. Exploring difference in effect of training whether on blood pressure regulating medicine or not, age, gender, and physical activity level (IPAQ). Finally, an analysis of variance (ANOVA) model will be applied after 10 weeks of training to explore if there exists a leveling-off effect on SBP in the IHG group.

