## Discussion

The aim of this randomized control trial is to explore whether 20 weeks of IHG home training on older adults (50 + years of age) with hypertension can reduce SBP compared to usual care. In order to increase the clinical value of this study, our inclusion and exclusions criteria are selected to target patients where lifestyle changes are recommended by national guidelines as first line therapy before initiation of medical treatment.

This study adds further knowledge to the current academic literature in several aspects. Firstly, the duration of the intervention in this study will be 20 weeks compared to the average durations of 7.5 weeks seen in previous studies with the longest reported study of 10 weeks. Secondly, with a longer study duration and measurements every 5 weeks, this study should be able to reveal when, and if, a possible leveling-off effect on measures of blood pressure occurs. Thirdly, the present study will extend the size of previous IHG training studies as former studies have included smaller sample sizes (on average approximately 28 participants) [9]. Fourthly, this is the first study to explore the effects on resting blood pressure using a standard Wii for IHG training. Finally, in the present study participants will perform home-based IHG training. Previous studies report IHG training taking place in either a hospital or university setting burdening participants with traveling time and changes in environment and potentially affecting their adherence to the training program. If the home-based IHG training is potent in lowering resting blood pressure this type of setup with home training could be attractive to many patient populations.

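### Ending follow-up when an anti-hypertensive drug is changed conflicts with the intention-to-treat analysis of SBP

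*Protocol article*

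**What the plan says.** All references are to the protocol article.

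- **Safety considerations, adverse events, and termination of study:** "Participants will be removed from the study if they start/adjust/terminate anti-hypertensive drugs during the trial". The next sentence puts this on the same footing as events after which no measurement is possible: "Likewise, if they die or emigrate they will be removed from the study".
- **Data analysis:** "statistical analysis will be conducted according to the intention-to-treat principal". A per-protocol analysis is added as a sensitivity analysis. Its set is defined by training sessions completed, and drug changes play no part in it.
- **Primary outcome measure and Data analysis:** "The primary endpoint in the study is SBP". The between-group difference in change from baseline to week 20 "for the primary endpoint will be analyzed using a linear mixed-effects model".
- **Assessment protocol:** after randomisation, "all participants will return to Aalborg University Hospital at weeks 5, 10, 15, and 20 for follow-up assessments".
- **Discussion:** the entry criteria target patients for whom "lifestyle changes are recommended by national guidelines as first line therapy before initiation of medical treatment".

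No section says that a participant with a drug change keeps attending, that later SBP readings are used, or whether readings already taken are kept.

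**The concern.** An intention-to-treat comparison needs week-20 SBP from everyone randomised, whatever happened to their treatment in between. The removal rule stops measurement after an event that is plausibly connected with the outcome. A drug may be started or increased because SBP stays high, and reduced or stopped because it has fallen. If training works, the first would be commoner under usual care and the second under training, so the two arms could lose different kinds of participant.

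Three things are at stake:

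- The primary comparison could be distorted. Losing usual-care participants with high SBP and training participants with low SBP pulls the estimate towards zero. Losing mainly training participants who did not respond inflates it.
- Harms are a stated secondary aim and are asked about at each follow-up visit. Removed participants are no longer asked.
- The removals use up, or add to, the 25% loss allowed for in the Sample size section. The text does not say which.

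**Working it through.** **Step 1. The text.** Follow what happens to a participant whose drug is changed at week 8.

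| Question | What the article provides |
|---|---|
| Is the week-5 SBP kept? | Not stated |
| Are weeks 10, 15 and 20 attended? | No; the participant is removed |
| Is there a week-20 SBP for the primary analysis? | No |
| Is this confined to the per-protocol analysis? | No; that set is defined by sessions only |

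The intention-to-treat value for this person, SBP at week 20 whatever drugs are being taken, is therefore never observed.

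**Step 2. Would the mixed model repair it?** If the earlier visits are kept, the model in effect predicts the missing week-20 value from participants who were not removed. This is unbiased only if removal depends on recorded SBP alone. Even then the prediction describes someone whose drugs did not change, so it answers a different question from intention-to-treat.

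**Step 3. Illustration of size.** The plan gives no rate of drug changes and so no figure to reproduce. From the Sample size section come a 7 mmHg difference in SBP change and SDs of 8 (training) and 9 (usual care). The 135–179 mmHg entry range comes from the inclusion criteria. Everything else is assumed:

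- Baseline B is normal, mean 150, SD 10, limited to 135–179.
- Week-20 change D = μ + s·c, with (μ, s) = (0, 9) in usual care and (−7, 8) in training.
- Interim change I = μ + s·(ρ·c + √(1−ρ²)·e), where c and e are independent standard normal and ρ is 0.5 or 0.8.
- A drug is changed with probability p (0.5 or 1) if B + I reaches the trigger T (160 or 165 mmHg).

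Three estimates are compared. *Dropped*: the difference in mean D among those not removed. *Earlier visits used*: within each arm, D regressed on B and I among those not removed, then predicted for everyone. *Intention-to-treat*: if a drug change lowers SBP by 8 mmHg (assumed), the effect is 7 − 8 × (r_C − r_T), where r_C and r_T are the proportions with a drug change in usual care and training.

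| T | p | Removed, usual care | Removed, training | Dropped, ρ = 0.5 | Dropped, ρ = 0.8 | Earlier visits used | Intention-to-treat |
|---|---|---|---|---|---|---|---|
| 165 | 0.5 | 7% | 2% | 6.8 | 6.6 | 7.0 | 6.6 |
| 165 | 1 | 14% | 4% | 6.5 | 6.1 | 7.0 | 6.2 |
| 160 | 0.5 | 12% | 5% | 6.7 | 6.5 | 7.0 | 6.4 |
| 160 | 1 | 24% | 10% | 6.2 | 5.7 | 7.0 | 5.8 |

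Entries are reductions in mmHg. Example for the last column: T = 160, p = 1 gives 7 − 8 × (0.243 − 0.097) = 5.8.

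**Step 4. Sensitivity.** With ρ = 0 there is no bias (7.0). Adjusting the dropped analysis for baseline gives 5.4 to 6.7. A trigger of 155 with p = 1 and ρ = 0.8 gives 5.3 unadjusted, with 38% of usual care and 19% of training removed. The simulation covers only drugs prompted by high SBP, so it shows only attenuation.

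**The case against.** The best defence is that removal may mean only the end of participation. Nothing in the article says that earlier readings are discarded, and a mixed model with visits at weeks 5, 10 and 15 can use them. When observed SBP drives removal, that analysis returned 7.0 in every scenario. Separating the training effect from drug changes is also a legitimate question. Drug changes may be few: treated participants must have had no treatment change for 4 months, and those with manifest cardiovascular disease, diabetes or SBP of 180 or more are excluded. Drugs can also change for reasons unrelated to SBP, such as side effects, and the article names no reason.

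Much of this stands, and it rules out three stronger readings that a reader might infer:

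- *That participants are deleted because of their blood pressure.* The text does not say that data are deleted, and the link with SBP is plausible but inferred.
- *That the effect is attenuated by 7–23%.* That range (6.5 down to 5.4 mmHg from 7.0) needs removal to be decided by the week-20 value itself and the person then to be dropped entirely. Someone removed before week 20 is removed on earlier information.
- *That following everyone would recover 7.0 mmHg.* It would not. On the assumed 8 mmHg drug effect, the intention-to-treat effect is itself about 5.8 to 6.6.

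The defence does not remove the conflict. The model-based answer is not an intention-to-treat effect. It also rests on a condition that the trial cannot verify, because readings outside the study may prompt a drug change. An unseen analysis plan could settle which readings are used, but not supply readings that the protocol stops collecting.

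**Conclusion.** The concern holds as a conflict between two stated rules: follow-up ends at a drug change, yet the main analysis is to be intention-to-treat. For participants with a drug change, the intention-to-treat outcome is not collected, and neither are later harms. This conclusion needs no assumption about numbers.

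The size and direction of any bias cannot be fixed from the article. With an interim trigger of 160–165 mmHg, 50–100% of those reaching it changing drugs, and a correlation of 0.5–0.8 between interim and week-20 change, dropping these participants entirely turns 7.0 mmHg into about 5.7–6.8 (unadjusted). Using earlier visits gives 7.0 if observed SBP drives removal. The 7.0 here is the effect without drug changes, so the shortfall should not be read as bias against the intention-to-treat effect. The case for change is that the stated analysis should be possible. It is not a promise of a larger effect or more power.

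**What to change.** Reconcile the Safety considerations and Data analysis sections by separating a drug change from the end of follow-up:

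1. Participants whose anti-hypertensive drugs change stay in the study, keep attending the remaining assessments at weeks 5, 10, 15 and 20, and are asked about harms as planned.
2. They are analysed as randomised, and the primary analysis uses all SBP readings, before and after the change.
3. The date and type of each change are recorded, and changes are reported by arm.
4. One supplementary analysis treats readings after a change as missing, described as estimating the effect had no drug been changed.

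Decisions on drugs and on continuing training remain clinical and are not part of this change.

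The cost is a revised sentence, one added analysis and the recording of drug changes. The visits are already scheduled, and according to Trial status recruitment has not yet begun. The downside is that the primary effect then includes the consequence of drug changes and may be smaller; the supplementary analysis addresses the other question.

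### Removal from the study after an anti-hypertensive drug change or death ends the scheduled harms enquiry, and deaths and drug changes have no stated place in the harms report

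*Protocol article*

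**What the plan says.** The Background section of the protocol article sets a secondary aim "to explore adherence and potential harms related to the IHG home training". The Abstract repeats the aim and says that harms will be reported.

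The section on safety considerations, adverse events, and termination of study gives two ways of learning about harms. First, "participants are encouraged to contact the study coordinator if they experience any side effects from the IHG training". Second, at the follow-ups at weeks 5, 10, 15 and 20, "all participants will be asked if they have any discomfort or encountered any harms by being part of the study". The section on secondary outcome measures adds a self-rated pain score for each hand after every training session.

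The same safety section then sets the removal rule: "Participants will be removed from the study if they start/adjust/terminate anti-hypertensive drugs during the trial". The next sentence reads: "Likewise, if they die or emigrate they will be removed from the study". Neither sentence makes an exception for continued safety follow-up. The Data analysis section says that "statistical analysis will be conducted according to the intention-to-treat principal".

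**The concern.** The rule removes people from the study, not merely from the training. Its main trigger is a change in blood-pressure treatment, in a trial whose primary endpoint is systolic blood pressure. Those who leave the harms enquiry are therefore selected by how their blood pressure was managed and are not a random subset. Death is handled administratively, alongside emigration. A start, change or stop of an anti-hypertensive drug, together with its reason, is informative for safety in such a trial, yet the text uses it only as a reason to remove.

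The harms result that the article promises is at stake. The point does not concern the analysis set for systolic blood pressure or the wording of the harms question.

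**Working it through.** The plan gives no figure on this point, so there is none to reproduce. The check compares the sections, followed by two small calculations that show what can and cannot be quantified.

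**1. Routes by which a harm can be recorded**

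| Route | Section | Who | What it covers | After removal |
|---|---|---|---|---|
| Contact with the coordinator | Safety considerations | In practice the training arm, since it concerns side effects of training | Self-reported side effects | Not stated |
| Question at weeks 5, 10, 15, 20 | Safety considerations | Both arms | Self-reported discomfort or harm | No visit is stated for a removed person |
| Pain score after each session | Secondary outcome measures | Training arm | Hand pain only | Stops when training stops |

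The visit question is the only stated route common to both arms. All three routes are self-report, so none can carry a death. The study must learn of a death or drug change in order to apply the rule, so the fact itself reaches the study. What is missing is a stated place for it, and for the reason behind a drug change, in the harms report.

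**2. Scheduled enquiries lost per removed participant**

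| Week of removal | Visits still to come | Visits lost if the harms question is still asked at the next visit |
|---|---|---|
| 0–5 | 4 | 3 |
| 5–10 | 3 | 2 |
| 10–15 | 2 | 1 |
| 15–20 | 1 | 0 |

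If removal is equally likely at any time (an assumption), the mean loss is (4 + 3 + 2 + 1)/4 = 2.5 of 4 enquiries. If the change comes to light at the next visit and the question is still asked there, it is (3 + 2 + 1 + 0)/4 = 1.5 of 4.

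**3. Effect on the number of harms recorded**

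Let f be the share removed, h_r and h_s the harm rates in removed and retained participants, and c the share of the removed participants' harms that is recorded. Then

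recorded / true = [f·h_r·c + (1 − f)·h_s] / [f·h_r + (1 − f)·h_s].

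The documents give none of these four quantities. The Sample size section assumes a 25% loss but does not say how much of it is removal. The table assumes h_r = 30% and h_s = 5%. For f = 10% and c = 0: true = 0.10 × 0.30 + 0.90 × 0.05 = 0.075; recorded = 0.90 × 0.05 = 0.045; ratio = 60%.

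| f | c = 0 (worst case) | c = 0.5 | c = 1 |
|---|---|---|---|
| 5% | 76% | 88% | 100% |
| 10% | 60% | 80% | 100% |
| 25% (all planned loss is removal) | 33% | 67% | 100% |

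If removed participants were no likelier to be harmed (h_r = h_s), the ratio at c = 0 would be 1 − f, that is 95%, 90% and 75%. The result depends heavily on c, which the text leaves open.

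**The case against.** The strongest reply is that the gap is read into a condensed article. The text does not say that earlier harm records are discarded, that the reason for removal goes unrecorded, or that the coordinator stops taking calls. Follow-up after withdrawal may be in the full protocol. This stands in part: nothing shows that harms before or at removal are lost. It does not dispose of the point, because the article states an unqualified rule of removal from the study, which, followed as written, ends the visits.

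A reader might infer three stronger things, and the documents support none of them.

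- *The harms report misses the people most likely to have been harmed.* A harm that precedes or prompts a drug change can be reported to the coordinator or at a visit. That removed participants were harmed more often is plausible but not stated.
- *The result is biased towards no harm.* Drugs may also be reduced or stopped because blood pressure fell, and changes can occur in either arm, so the direction is not established. An example in which every harm among removed participants vanishes is the c = 0 worst case and assumes the point in dispute.
- *The safety section contradicts itself.* The promise to ask all participants can be read as all who attend, in both arms. It is unclear beside the removal rule but not strictly inconsistent with it.

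Two further replies carry some weight. The aim concerns harms related to the training, and no formal between-arm harms comparison is specified. Serious events should also be few. The section on participants and setting targets a 10-year risk of stroke or myocardial infarction of 15–20%. At a constant rate, the 20-week risk is 1 − 0.85^(20/520) ≈ 0.6% to 1 − 0.80^(20/520) ≈ 0.9% per person, or about 0.3 to 0.4 events among 50. That limits the expected number of such events. It says nothing about drug changes, and it makes each event that does occur more important to report.

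**Conclusion.** The concern holds in a limited form. The removal rule ends the scheduled harms enquiry for participants selected by a change in blood-pressure treatment, and it leaves deaths and reasons for drug changes without a stated place in the harms report. The loss consists of harms arising after removal and of the by-arm account of deaths and drug changes.

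Per removed participant, between none and four of the four scheduled enquiries are lost, averaging 1.5 to 2.5 if removal times are uniform. The effect on the harms result cannot be computed in size or direction; the recorded shares above rest on assumed rates. The conclusion takes removal from the study at its ordinary meaning. If the full protocol keeps safety follow-up after removal, the remedy reduces to saying so. The point should be settled before recruitment, which the Trial status section describes as about a month away.

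**What to change.** In the section on safety considerations, adverse events, and termination of study:

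1. State that removal does not end harms follow-up.
2. Continue the scheduled harms question to week 20 for every randomised participant who can be reached, by visit or telephone.
3. Record each start, adjustment or stop of an anti-hypertensive drug with its reason, and each death, and report these by arm over all randomised participants.

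This changes data collection and reporting only; no treatment rule is altered or proposed. It costs a sentence or two in the protocol, one data-capture form, and a few short calls per removed participant. The Assessment protocol section already has the coordinator telephoning participants before measurements. The downside for the sponsor is a possibly less favourable harms table.
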